***Map 1: All 11 Study Districts & Locations*** ***Map 2: Eligible & Excluded Locations***

***Map 3: 45 Selected Locations*** ***Map 4: The 4 Study Arms***

**Figure 2:** Maps 1-4 showing selection steps

**Table 3:** Randomization schedule for selected Locations

| **DISTRICT** | **LOCATION NAME** | **STUDY ARM** | **Study Region** |
| --- | --- | --- | --- |
| Ndhiwa | Central Kabuoch | IPC arm | 1 |
|  | Central Kanyamwa | Control arm |  |
|  | Central Kanyidoto | IPC and DSO arm |  |
|  | East Kwambwai | DSO arm |  |
|  | North Kanyamwa | DSO arm |  |
| Homa-Bay | Gem West | IPC arm |  |
|  | Homa Bay Township | Control arm |  |
|  | West Kochia | DSO arm |  |
|  | Gem East | DSO arm |  |
|  | Gongo | IPC and DSO arm |  |
| Suba | Gembe East | Control arm |  |
|  | Gwasi North | IPC arm |  |
|  | Gwasi South | DSO arm |  |
|  | Kaksingri East | Control arm |  |
|  | Rusinga West | DSO arm |  |
| Kisumu East | West Kolwa | DSO arm | 2 |
|  | Central Kisumu | DSO arm |  |
|  | East Kolwa | IPC and DSO arm |  |
|  | Kawino | Control arm |  |
| Kisumu West | N.C Seme | Control arm |  |
|  | North-West Kisumu | IPC arm |  |
|  | S.W. Seme | IPC and DSO arm |  |
| Migori | Lower Suna | IPC and DSO arm | 3 |
|  | Suna East | Control arm |  |
| Nyatike | East Karungu | IPC arm |  |
|  | Kaler | Control arm |  |
|  | West Muhuru | IPC and DSO arm |  |
|  | North Kadem | IPC arm |  |
|  | South East Muhuru | DSO arm |  |
|  | West Kadem | IPC and DSO arm |  |
| Rongo | West Sakwa | IPC and DSO arm |  |
|  | Lower Kanyamkago | IPC arm |  |
|  | West Kanyamkago | IPC and DSO arm |  |
| Bondo | Central Sakwa | DSO arm | 4 |
|  | East Yimbo | IPC arm |  |
|  | North Sakwa | Control arm |  |
|  | West Yimbo | IPC and DSO arm |  |
| Rarieda | South Asembo | Control arm |  |
|  | West Uyoma | IPC arm |  |
| Siaya | West Gem | IPC and DSO arm |  |
|  | West Uholo | IPC arm |  |
|  | N.West Gem | IPC and DSO arm |  |
|  | S.W. Alego | Control arm |  |
|  | Township | DSO arm |  |
|  | Ukwala | IPC arm |  |

1. Random selection of participating Villages from each of the 45 study Locations: According to the 2009 Kenya population census report, the selected 45 study Locations have a total of 165,514 households divided into 1,312 Villages. The three steps below describe the process of selecting representative Villages from each of the 45 Locations that will participate in the study:
   1. Since the census report does not provide population data by age at the Location level, we used the number of households (HH) and number of men in our target group (25-39 years) at the district level (2009 census) to calculate the average # of men aged 25-39 years per 100 HH (column 4 Table 4).
   2. Using the average # of estimated men aged 25-39 years/100 HH by districts in (a) above, we estimated the population of uncircumcised men aged 25-39 years in the 45 study Locations (column 3 table 5) and used this to calculate the # of men to be contacted per study Location (column 4 table 5) using probability proportion to population size.
   3. We then used the above information to estimate the # of HH to be visited (column 5 table 5), which allowed us to arrive at the number of participating Villages to be selected (column 6 table 5).

**Table 4:** Average # Men Aged 25-39/100 Households

| District | Population aged 25-39 | No of HHs | Average no of men (25-39)/100 HH | Average (men 25-39 yrs) non-circumcised /100 HH |
| --- | --- | --- | --- | --- |
| Bondo | 14288 | 37296 | 38 | 27 |
| Homa Bay/Ndhiwa | 25123 | 79540 | 32 | 22 |
| Kisumu East | 55666 | 115502 | 48 | 34 |
| Migori/Nyatike | 26648 | 70516 | 38 | 26 |
| Suba | 18769 | 45320 | 41 | 29 |
| Kisumu West | 9850 | 32992 | 30 | 21 |
| Rongo | 24937 | 67895 | 37 | 26 |
| Siaya | 36997 | 130705 | 28 | 20 |
| Rarieda | 9888 | 31033 | 32 | 22 |
| Total | 222166 | 610799 | - | - |
| Average | - | - | 36 | 25 |

**Table 5:** Estimated Target Population and # of Selected Villages

| **District** | **Location Name** | **# of Villages** | **Population uncircumcised aged 25-39 yrs** | **# of men to be contacted / Loc.** | **# of HH to be Visited** | **# Villages Selected** |
| --- | --- | --- | --- | --- | --- | --- |
| Ndhiwa | Central Kabuoch | 9 | 957 | 142 | 569 | 2 |
|  | Central Kanyamwa | 12 | 703 | 104 | 417 | 2 |
|  | Central Kanyidoto | 15 | 252 | 37 | 150 | 2 |
|  | East Kwambwai | 28 | 754 | 112 | 448 | 4 |
|  | North Kanyamwa | 16 | 435 | 65 | 259 | 3 |
| Homa-Bay | Gem West | 29 | 639 | 95 | 379 | 4 |
|  | Homa Bay Township | 40 | 1,957 | 291 | 1162 | 6 |
|  | West Kochia | 29 | 314 | 47 | 186 | 4 |
|  | Gem East | 15 | 567 | 84 | 337 | 2 |
|  | Gongo | 8 | 337 | 50 | 200 | 2 |
| Suba | Gembe East | 23 | 782 | 116 | 465 | 4 |
|  | Gwasi North | 42 | 926 | 138 | 550 | 8 |
|  | Gwasi South | 19 | 559 | 83 | 332 | 4 |
|  | Kaksingri East | 28 | 407 | 60 | 242 | 5 |

# PHASE 1: HOUSEHOLD ENUMERATION

To ascertain the size of eligible population (uncircumcised men aged 25-39 years), we will conduct complete household listing in all selected villages and enumerate male members in each household aged 25-39 years (Appendix 1: Household Enumeration Form). During this exercise, we shall physically visit all homes in the study villages and assign a unique identification number to every household (HIN ), which will be preceded by a pre-assigned study Location and village codes (e.g., KAW/KOD/1234 for Kawino Location and Kodongo village and Household number 1234). Enumeration shall be through home visits ONLY and not by any other means. The unique HIN assigned during the enumeration will be entered on Excel database and households with men aged 25-39 years will be sorted out and put on a separate list. The names and identifying information shall be kept separately from the main database (in a locked, password protected file) and will not be accessible to the person(s) working on the analysis.

Names of heads of household: We shall obtain names of heads of households during enumeration to help us identify selected households when we return for screening and enrollment. In this community, homes are identified using names of household heads. As such these names will be entered in the database. However, they will not be used for any analysis. Access to this data will be pass-word protected and restricted to the data manager and other authorized staff only. This information is strictly for purposes of locating the homes for the return visits to consent and enroll participants, to collect baseline and endline data, and to implement the intervention. Because of the expansive geographical coverage of study sites, we will organize coordination in 4 regions as in Table 3 above, based on proximity and logistics. Each Region will have a coordinator responsible for study activities on a day-to-day basis and reporting to the Study Coordinator. At the regional offices, we will have a data office for entry of data collected in the respective regions; the officer will be reporting to the data manager at the head office. Both at the study coordinating center in Kisumu and the regional offices, data will be entered in password-protected computers and stored in locked room accessible to data staff, regional coordinators, data manager and PIs. After data submission to the head office in Kisumu (using a password-protected flash drive), only the PIs, data manager, study statisticians and study coordinator will have access to the consolidated data base.

Because of the non-intrusive nature of the data to be collected, we shall obtain oral consent from the head of household or any adult member who can give us information on only the age and sex of household members. We therefore request for a waiver of documentation of written consent.

At this visit we will also collect names and telephone numbers (where known/available) of men aged 25-39 years to help us prepare a list of those to be reached by the intervention and contact them by phone or home visit to make appointments for baseline survey. We will also collect locator information of households with men aged 25-39 years, to guide the study staff who will return later for enrolment visit. At the end of the household enumeration, the data manager will prepare a complete listing of potentially eligible men in an excel sheet and the RAs will visit everyone in this list. During enrollment the RA will administer consent, assign Participant Unique ID (see pg xx), conduct baseline interview and verify the MC status of consented participants.

The list will be used to create a log of eligible men in each village. Determining the number of households with eligible men will help in knowing the denominator and in planning for recruitment. Once this information is obtained, we will use it to start planning for Phase 3 of the study (Conducting Rapid Formative Study). Phase 2 (Establishing Baseline VMMC Prevalence and Proportion of Eligible Men) of the study, described here below, will be implemented concurrently with Phase 1. In addition, we have drafted the tool [to be known as *VMMC Demand Creation Tool*] which will be used for demand creation in IPC and IPC+DSO Locations. Before being used, this tool will be updated with information collected from the formative phase of the study and submitted to the two IRBs for approval prior to implementation. We have attached herewith the draft version for initial review (Appendix 16: VMMC Demand Creation Tool). All eligible men in the selected villages will be approached to join the study.

# PHASE 2: CONDUCTING RAPID FORMATIVE STUDY (SUB-STUDY 1)

**Justification:** This phase is intended to provide information for use in delivering the interventions. We have already drafted messages based on existing literature for use in IPC and IPC+DSO intervention Locations/villages. However, since almost all the available information on barriers to and facilitators of VMMC in literature were collected among men of all ages and were not disaggregated by age group,^21,23^ we cannot assume they are automatically relevant to older men. As such, it will still be necessary to conduct a rapid formative study to explore reasons why older men aged 25-39 years go or do not go for VMMC services. Information obtained from this phase will be used to modify, if indicated, the messages developed from existing literature. We wish to emphasize that only systematic review and drafting of messages will be done while we await ethics approval for the messages, and certainly no data collection will be done before obtaining ethics approvals from both KNH-ERC and CDC IRB.

## SUB-STUDY DESIGN

This phase shall comprise of Focus Group Discussions (FGDs) and In-Depth Interviews [[4](#_ENREF_4)]. Twelve FGDs, with 6-10 participants, will be held with six groups of circumcised men and six groups of uncircumcised men, as follows:

- 1. 25-29 in southern Nyanza
  2. 30-34 in southern Nyanza
  3. 35-39 in southern Nyanza
  4. 25-29 in northern Nyanza
  5. 30-34 in northern Nyanza
  6. 35-39 in northern Nyanza

Similarly, twelve FGDs, with 6-10 participants, will be held with six groups of female partners of circumcised and six groups of female partners of uncircumcised men to obtain information to be used if men come with their female partners during the intervention or raise issues about women and VMMC. We will also use the FGD sessions to confirm the suitability and completeness of the messages we shall have developed from existing literature on demand creation.

Besides FGDs, we will conduct 48 IDIs to capture confidential information that some men and women would otherwise not divulge in an FGD setting. The IDI with male participants will comprise of four circumcised men and four uncircumcised men in each of the following age categories: 25-29 years, 30-34 years and 35-39 years. The IDIs with circumcised men and their partners will explore the same issues as the FGDs but with more specific questions about respondents’ experience at the circumcision site during service provision and sexual behavior post-MC (circumcised group, Appendix 9 & 12). For uncircumcised participants, specific questions will explore barriers within the families (e.g., with spouses, parents, children, siblings) or among friends and peers, as well as perceptions of the effect of VMMC on sexual performance (Appendix 10 & 13).

The IDIs with female participants will comprise of four partners of circumcised men and four partners uncircumcised men in each of the following age categories: 25-29 years, 30-34 years and 35-39 years.

We will also use the FGDs and IDIs to identify key and preferred sources of information on VMMC; which information type and source appeal to older men, which ones do not and why; and what messages convinced (if circumcised) or would convince (if uncircumcised) them and/or their peers to take up VMMC. To help in selecting appropriate people to serve as recruiters or service providers, we will collect their views on preferred characteristics (e.g., age, sex, etc). We will also obtain information on appropriate forums and strategies to reach older men with VMMC information one-on-one or in small group (e.g., work place, home, place of worship, etc).

The FGDs and IDIs will be conducted by trained study staff, with at least a diploma in social sciences or related field, and two years of research interviewing experience. They will be trained on ethics and protocol, and taken through intense practice with the guides until they become competent. The interviewers will be same gender as participants and fluent in English and the local language (*Dholuo*). Both FGDs and IDIs will take approximately one and a half hours.

**Inclusion/Exclusion Criteria**

***Focus Group Discussions and In-depth Interviews***

*Male participants:*

Inclusion:

- Aged 25-39 years
- Discloses status as circumcised or uncircumcised
- Gives consent to participate in the FGD and be audio-recorded.
- Resident of any of the 77 Locations outside main study area, within the 11 study districts.

Exclusion:

- Outside the 25-39 years age bracket
- Does not disclose circumcision status
- Non-resident of any of the 77 Locations outside main study area, within the 11 study districts.
- Declines to consent to participate in the study

*Female participants* [these are general women reporting having circumcised or uncircumcised partners, and not necessarily partners of men above]:

Inclusion:

- Aged ≥18 years
- Discloses that their partner’s circumcision status
- Gives consent to participate in the discussion and be audio-recorded.
- Resident of any of the 77 Locations outside main study area, within the 11 study districts.

Exclusion:

- Below 18 years of age
- Does not disclose circumcision status of partner
- Not resident of any of the 77 Locations outside main study area, within the 11 study districts.
- Declines to consent to participate in the study

### Selection of the FGD/IDI Locations and Participants

The formative study Locations will be selected as follows:

- The FGDs will be done in both southern and northern Nyanza regions. After systematic elimination by factors such as proximity to circumcising communities, multi-ethnic urban populations, and geographical inaccessibility, 122 administration Locations were potentially eligible for inclusion in the study; of these, 45 that were not adjacent to each other were selected, leaving out 77 Locations. The FGDs and IDIs will be conducted in some of the 77 Locations which were otherwise eligible but not selected for study due to geographical proximity to those selected. The process of selection will be done as follows:
  - 36 Locations (18 in Southern and 18 in Northern Nyanza) will be randomly selected out of the remaining 77 eligible Locations that were not selected for the implementation of the interventions.
  - 12 FGDs and 24 IDIs (divided equally between men and women) will be conducted in each of the regions - Southern and Northern Nyanza.
  - In each Location, various opinion leaders will be identified and asked to refer one eligible male and female participant for either IDI or FGD, until the required sample size is reached. The opinion leaders will include Chiefs, Assistant Chiefs, Village Elders, teachers, religious leaders, male group leaders, etc. This will ensure a variety of nominees.

### Consenting

We will obtain Written consents (Appendix 4: Written Informed Consent for FGD with Circumcised and Uncircumcised and Appendix 6: Written ICF for Main Study FGD with Partners of Circumcised and Uncircumcised Men) to conduct FGDs using standard guides (Appendix 5: FGD Guide for Circumcised and Uncircumcised Men and Appendix 7: FGD Guide for Partners of Circumcised and Uncircumcised Me). We will also obtain written informed consents (Appendix 8: Written ICF for IDI with Circumcised and Uncircumcised Men and Appendix 11: Written ICF for IDIs with Female Partners) to conduct IDIs with circumcised men (Appendix 9: In-Depth Interview Guide for Circumcised Men) and uncircumcised men (Appendix 10: In-Depth Interview Guide for Uncircumcised Men), partners of circumcised men & partners of circumcised men (Appendix 12: In-Depth Interview Guide for Female Partners of circumcised Men) and partners of uncircumcised men (Appendix 13: In-Depth Interview Guide for Female Partners of Uncircumcised Men). Recruitment of participants and their composition are described in detail above. The study will be done to confirm barriers to and facilitators of VMMC uptake relevant to older men, from the perspective of both men and women. In addition, this phase will serve to identify appropriate VMMC messages and delivery forums for the target age group.

### Procedure of the FGD

The FGDs will be conducted with both circumcised and uncircumcised men. There shall be a moderator and the note taker who will document observations during the discussions. The group shall consist of 6 – 10 participants and will use the local language (*Dholuo*). There shall be an instruction manual attached to the questionnaire guide for the moderator to use.

Before starting off, the research assistant will:

1. Introduce self and clearly explain that this discussion is part of a research study on voluntary medical male circumcision (VMMC) to better understand what would make more men aged 25 to 39 years go for VMMC and that the discussion would take approximately 1½ hours;
2. Obtain a individual written consent and brief demographic information as participants come in;
3. Assign each participant a serial number for use when contributing to the discussion during the FGD, and issue number tags. Explain that this is necessary to make it easy for the researchers to follow the views contributed by each person while keeping personal identity confidential. Urge participants to not reveal names and personal details during the session;
4. Explain that the discussion will be audio-recorded to capture all contributions from participants, that audio tapes will be destroyed (digital recorders erased) after transcription (by the study coordinator and witnessed by the data manager) and that the recordings will not be used for any other purposes. Emphasize need to not mention name while recording is taking place;
5. Emphasize that taking part in the group discussion is voluntary and those not willing to be audio-taped are ineligible;
6. Confirm the audio-recorder is functioning, and switch it on for the discussion to start.

Data from the FGDs and IDIs will be transcribed, typed, coded and analyzed to extract information on top barriers to and facilitators of VMMC among older men. The results will be reviewed for concurrence with existing literature by the two PIs, together with the Nyanza-based co-investigators. The draft *VMMC Demand Creation Information Sheet for Older Men* developed with information from previous studies will be updated to incorporate any new information from the Formative Phase, **and submitted to KNH-ERC and CDC IRB for review and approval prior to implementation**.

While the recruitment message document (Appendix 16: *Toolkit for Addressing Barriers and Facilitators to VMMC*) will be undergoing ethical review, we will be setting up for the implementation of Phase 3 of the study.

# PHASE 3: ESTABLISHING BASELINE VMMC PREVALENCE AND PROPORTION OF ELIGIBLE MEN

Based on the eligible participants’ list, research assistants will only go back to households with men aged 25 to 39 years. Before administering enrolment consent, RAs will ask participants to identify a private location within or outside the house where they can do consenting and interviewing. The RA will then administer consent for participating in the study, enroll consenting participants (Appendix 2A: Written ICF for Enrollment and Verification of MC Status) and assign Participant Unique ID number. The number will comprise of the participant’s Location and Village codes, the first initials of the participant’s 3 names and a six digit number, preferably the last six digits of the participant’s national ID or telephone number, or another number selected by the participant if either of the national ID or telephone number is unavailable. These components will form the Participant Unique ID number. For example, Edward Albert Sungu from Kawino Location, Kodongo Village with 123456 as his six digit number, will have a Participant Unique ID number that will look like this: KAW/KOD/ E12/A34/S56.

At enrollment, participants will be given 3 months within which to go for circumcision, Participants can go whenever they want for VMMC, but our study will only capture their data if they go within 3 months. They will also be informed that a reminder of the expiry date for circumcision will be sent through text message to all participants one month before the expiry of the circumcision window period. The message will read: “***One month remaining. Take action for your health now***”. Participants will be informed at enrollment that they will be sent a text with the 3 words as a reminder that in case they have not gone for circumcision, they have 1 month remaining. This information has been captured in Written Informed Consent Form for Enrollment and Verification of Circumcision Status (Appendix 2A) as follows: **You have up to 3 months within which to go for circumcision. However, you are encouraged to go for circumcision as soon as possible; we recommend that it be within the next 3 months. Two months from now, you will be reminded through a text message to go for circumcision. The message will read: “*One month remaining.*** ***Take action for your health now*”.** The message is general and safe to receive even through a friend’s phone for those who do not own phones. A reminder is important because in an ongoing study on demand creation for VMMC in Kenya (funded by the Bill and Melinda Gates Foundation), preliminary results from the qualitative component reveal that participants who did not go for circumcision wished they were reminded because they simply forgot.

After assigning the participant unique ID number, the RA will conduct the baseline interview (Appendix 2B: 2 Questions for All Clients aged 25-39 yrs at Counseling), verify the MC status and inform participants of their intervention arm and deliver the intervention if participant is available (if not, another visit will be made at a later date to deliver the intervention). During the interview, we will document participants’ circumcision status from verbal report. After the interview, participants who consented to physical examination will be asked to choose where this can be performed. The identified location shall be acceptable to both the participant and RA. Physical verification will be done to minimize mis-reporting and/or misclassification, especially by those who are partially circumcised or who were born with short foreskins. Circumcision status will be recorded as fully circumcised (no foreskin), partially circumcised (foreskin is past corona sulcus but covers less than one half of the glans, in a flaccid state), and fully uncircumcised (foreskin covers half or more of the glans, in a flaccid state) and recorded on Appendix 2B.

We estimate that consenting will take about 30 minutes, the interview will take about 45 minutes, penile inspection will take about 5 minutes, altogether approximately 1½ hours. Where the participant is ready for the intervention, the RA will proceed to provide the intervention given that the participant will have consented to it. The delivery of the IPC and IPC/DSO intervention will take additional 1 hour while in DSO-only Locations; the process will take additional 30 minutes. Where a participant does not have time, another visit will be made (see Phase 4 below).

Details of participants enrolled in the study will be entered into an excel Master Log (Appendix 14) which will contain all participant details; 3 names, ID number, age, location, village, telephone number of the participants or of close friend and date of enrollment.

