Recruitment Approach: Depending on participant’s availability, this phase can be conducted together with Phase 2 if the intervention tool (Appendix 6) has been approved, and done subsequent to verification of MC status; alternatively, another visit will be made if participants do not have time or if Appendix 6 has not been approved. If another visit is needed, we will visit every household with enrolled participants at a time when they are likely to be at home (with their spouses where applicable) to discuss VMMC using the demand creation tool (Appendix 16: *VMMC Demand Creation Tool kit*) as described in the next sub-section.

Participants in IPC or IPC/DSO Location will receive information on VMMC while those in DSO Locations will be informed about, and given directions to VMMC sites designated to older men. During consenting, participants will be informed that by consenting to be enrolled in the study, they are consenting to be assigned into one of the three intervention arms or control. Hence, by consenting to join the study they will also have consented to participating in the respective interventions. After delivering the intervention (whether at enrollment visit or a subsequent one), participants will be given a pre-designed referral coupon (Appendix 15: Referral Coupon) to take along when going for services. They will also be asked to memorize the serial number if possible. The RAs will be expected to return to the same households up to three times (within a period of three month) to reach those not found at home during the previous visit – this applies to both enrollment visit and the visit to deliver the intervention, if different from enrollment visit.

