# PHASE 5: ESTABLISHING ENDLINE MC UPTAKE/ESTIMATING IMPACT OF INTERVENTIONS

At Endline, we will review our Participants Master Log (Appendix 14) to identify those who did not go for VMMC at the 45 VMMC clinics participating in the study. We will use the telephone numbers obtained during enrollment to contact the participants. Those who say that they got circumcised but are not in our Participant Master Log, we will make an appointment and visit them at home, or another convenient location, to administer consent (Appendix 2C), conduct Endline interview (**Appendix 2D: Phone and In-Person Interview with Uncircumcised Men at Endline**) and verify their circumcision status. Those who report not having gone for VMMC will be asked why they did not go, and their response recorded in Appendix 2D. If more than one reason is given, the participant will be asked to rank the top three reasons from most to least important. As enrolled participants go for VMMC services, we will be recording in the study’s Participants Master Log that they have been circumcised. However, only those who go for VMMC at study-designated clinics where we have stationed Research Assistants to monitor uptake will be recorded in the Participants Master Log. Recognizing that some participants could choose to go for circumcision in non-study clinics, we will need to capture those ones as well. To do this, we will not call any person apart from men who are listed in our Participants Master Log. We will review VMMC program theater registers in non-study clinics located within the 12 districts where the study is being conducted and compare the names with those indicated on the Participants Master Log as having not gone for VMMC. For those where the three names of VMMC clients in theater registers match the three names in the Participants Master Log, we will contact them using the phone numbers registered in the Participants Master Log and NOT in VMMC theater registers. When calling, the TASCO participants who could have been circumcised at non-study clinics will be asked if they were enrolled in the study. If they were, we will schedule a visit at home and obtain consent and if willing, conduct endline survey and verify MC status; if not, they will not be contacted further.

Inclusion/Exclusion Criteria

Inclusion:

- - 1. Was enrolled in the main study
    2. Resident of the study village
    3. Did not go for circumcision per TASCO Study database

Exclusion:

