|  | Implement the three interventions, including collecting information on costing and specimens for unlinked HIV testing. ***Approx. 9 Months*** |  |  | |  | | **x** | | **x** | **X** |  |  |
| **Phase 5** | Carry out endlline survey in all households with men 25-39 years uncircumcised at baseline; interview them; verify their MC status and use baseline data from men aged 25-39 years to determine the impact of the interventions. ***Approx. 3 Months*** |  |  | |  | |  | |  | **x** | **x** |  |
| **Cross-cutting** | Data entry, cleaning and analysis, report writing and manuscripts preparation. ***Ongoing up to 18 Months*** |  |  | | **x** | | **x** | | **x** | **x** | **x** | **x** |
|  |  | | | | | | | | | | | |
| **Sub-Study 4** | Develop SOPs; prepare logistics such as printing study materials. ***Approx. 2 Months*** |  | |  | |  | | **x** |  |  |  |  |
|  | Hire and train RAs. ***1 Month*** |  | |  | |  | | **x** |  |  |  |  |
|  | Enroll male participants in the study. ***Up to 6 Months*** |  | |  | |  | |  | **x** | **x** |  |  |
|  | Follow up male participants. ***Up to 8 Months*** |  | |  | |  | |  | **x** | **x** | **x** |  |
|  | Enroll female partners of the men in the study. ***Up to 6 Months*** |  | |  | |  | |  | **x** | **x** | **x** |  |
|  | Data entry and analysis; manuscripts preparation. ***Ongoing up to 12 Months*** |  | |  | |  | |  | **x** | **x** | **x** | **x** |

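### The 3-month capture window starts at enrolment in every arm, but intervention delivery may come later, and nothing applies the 3-month limit to circumcisions found at endline

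*Protocol*

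**What the plan says.** **Window.** Protocol, Phase 3: "At enrollment, participants will be given 3 months within which to go for circumcision", and "our study will only capture their data if they go within 3 months". The consent wording fixes the same origin: "Two months from now, you will be reminded through a text message to go for circumcision", with one month then remaining. No passage restarts the clock at delivery.

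**Delivery.** Phase 3 has the research assistant deliver the intervention at the enrolment visit if the man is available; "if not, another visit will be made at a later date to deliver the intervention". Phase 4 (Recruitment Approach) adds that "another visit will be made if participants do not have time or if Appendix 6 has not been approved". That sentence calls Appendix 6 the intervention tool; elsewhere the toolkit is Appendix 16, and I read the two as the same document. Staff may "return to the same households up to three times (within a period of three month", and this is said to cover the delivery visit as well as the enrolment visit. The DSO section also allows a visit after enrolment. Control men are reached only at enrolment, with the standard booklet.

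**Timetable.** Table 8 marks baseline interviews in months 7-12 and implementation in months 10-18.

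**Endline.** Phase 5 calls enrolled men who are not recorded as circumcised and searches theatre registers of non-study clinics: "Those who say that they got circumcised but are not in our Participant Master Log, we will make an appointment". Table 8 describes the task as "Carry out endlline survey in all households with men 25-39 years uncircumcised at baseline", marked in months 16-21. Table 7 uses endline to count the men circumcised over the course of the study. Data Analysis says that the date and place of circumcision are collected.

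**The concern.** Uptake is the main outcome, so its time frame has to be unambiguous and has to give each intervention a fair chance to act. Two things stand in the way.

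First, the clock runs from enrolment while exposure may begin later, and only in the three intervention arms. Any time before delivery is control-like time counted in an intervention arm. A null IPC result could then mean that IPC does not work, or that it arrived when little of the window was left. The analysis cannot restore exposure time lost in this way.

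Second, the 3-month capture rule and the endline count do not share a stated cut-off. Without one, men followed for 3 months and men followed for longer can be mixed in one proportion, and it is unclear which effect the trial estimates.

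**Working it through.** **1. Time left after delivery.** With a window of 3 months from enrolment and delivery *d* months after enrolment, exposed time is 3 − *d*.

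| Situation allowed by the Protocol | *d* | Exposed time |
|---|---|---|
| Delivered at the enrolment visit (default) | 0 | 3 months |
| Delivered at the end of the three-month revisit period | 3 | 0 months |
| IPC arms, enrolled before toolkit approval | no stated limit | may be 0 |
| Control, booklet at enrolment | not applicable | not affected |

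Table 8 agrees. A man enrolled at the start of month 7 has a window covering months 7, 8 and 9, and implementation is first marked in the block for months 10-12. The blocks are three months wide, so this shows what the timetable permits, not what is typical.

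**2. The plan's sample size.** Inputs from Sample size Determination: 30% against 40%, two-sided alpha 0.017, power 80%, design effect 2.5. The pooled-variance two-proportion formula gives 473 per arm. The continuity correction gives (473/4) × [1 + √(1 + 4/(473 × 0.10))]² = 493. Then 493 × 2.5 = 1232.5, which rounds up to the stated 1233. For 30% against 45% the same steps give 229 × 2.5 = 572.5, so 573 as stated. The contact figure is 1233 × 1.30 = 1603. The only inflations are clustering, refusal and loss. None is for shortened exposure.

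**3. Illustration of dilution.** The documents do not give the share of men reached late (*f*) or the effect that they lose. Assume that late men lose half the effect:

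difference = 10 × (1 − 0.5*f*) points

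Power uses effective n = 1233/2.5 = 493 per arm, alpha 0.05/3 and control uptake of 30%.

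| *f* | Difference | Power, no continuity correction | Power, with correction |
|---|---|---|---|
| 0 | 10.0 | 82% | 80% |
| 20% | 9.0 | 72% | 70% |
| 33% | 8.4 | 65% | 62% |
| 50% | 7.5 | 54% | 51% |

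At *f* = 10% the uncorrected power is still about 77%.

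**4. How much a given delay costs.** Assume that 30% and 40% are 3-month figures reached at constant monthly rates: −ln(0.7)/3 = 0.119 and −ln(0.6)/3 = 0.170. With delay *d* for every man in an intervention arm, uptake is 1 − exp[−(0.119*d* + 0.170(3 − *d*))]. This gives 36.8% at 1 month (power 45%), 33.5% at 2 months (11%) and 30.0% at 3 months (no effect left). A delay of 1.5 months gives 35.2%, about half the effect, which matches the assumption in step 3.

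**5. Why the endline cut-off matters.** On the same rates, control uptake after 9 months is 1 − 0.7³ = 66%. The intervention arm reaches 1 − 0.6³ = 78% if the effect lasts (difference 13 points), or 1 − 0.6 × 0.7² = 71% if it stops at 3 months (difference 5 points). Against 10 points at 3 months, the target of estimation changes with the window.

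**The case against.** Delivery at the enrolment visit is the default, and later visits are the exception. The revisit rule is aimed at men not found at home, and repeat visits before a man is enrolled use none of his window. Enrolment date, clinic circumcision date and endline date are all collected, so one cut-off can be applied in analysis, perhaps in a statistical analysis plan that is not shown. The dilution runs towards no effect and does not manufacture a positive result. Some delay in reaching men can be seen as part of the strategy under test.

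Much of this stands, and it limits the size of the problem. It does not remove it. Waiting for ethics approval of a toolkit is a feature of trial start-up, not of the strategy. A later analysis document can choose a cut-off, but it cannot give back window time that passed before delivery.

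Four stronger readings are tempting, and the documents do not support them:

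- *IPC may be delivered before its toolkit is approved.* Phases 1 and 2 require approval by both review boards before use. Only enrolment, and so the clock, may precede approval.
- *The arms have different windows.* The nominal window is the same in all arms. Only the time left after delivery differs.
- *Study clinics stop counting at 3 months while other sources go on.* The capture rule in Phase 3 is study-wide, and Phase 5 states no 3-month stop for the clinic log. The gap is that no passage applies the limit to endline or register data.
- *DSO steers men to study-run sites, so capture differs by arm.* Phase 5 has 45 participating clinics for the 45 Locations, and men in both DSO arms are told that other sites remain open to them. No passage says that men in other arms use non-study clinics more.

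**Conclusion.** The point holds in this form: one nominal 3-month window from enrolment, delivery that may be deferred within or beyond it in the intervention arms only, and no stated date limit on circumcisions found at endline. The direction of the first effect is clear: it biases towards no effect, most in IPC and IPC+DSO. Its size is not known. It depends on the share of men reached late and how late, neither of which the documents give, so the fall in power to between 72% and 54% is an illustration under stated assumptions and not a forecast. These figures also take over the Protocol's design effect of 2.5. The endline gap is one of definition: the date needed to close it is already collected, but no rule says that it will be used.

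**What to change.** - Define the primary outcome as verified circumcision dated within one fixed window with one time origin, applied identically to all arms and to all sources: clinic log, theatre registers and endline.
- Do not start enrolment in any arm until the IPC toolkit is approved.
- Deliver at the enrolment visit where possible. Where later delivery visits remain allowed, set the common window in all arms long enough to run past the last permitted visit. For example, three months of revisits plus three months of exposure is six months, inside the nine months of residence that eligibility already requires.
- Align the consent and reminder wording in Phase 3, the revisit rule in Phase 4, the endline text in Phase 5, and Tables 7 and 8 with that window. State the 30% and 40% of the sample size for it.
- Record the delivery date for each man, and report circumcisions after the window as a secondary outcome.

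The cost is protocol and consent amendments, a possible short delay to enrolment, and a somewhat longer window. Circumcision dates are already collected; a delivery date adds at most one field to the visit record.
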